### Eligibility

Participants will be eligible for enrolment if they meet the following requirements:

#### Inclusion criteria

Women aged 25–40 yearsWho are willing to provide written informed consent to participate in the clinical trialA confirmed diagnosis of DOR fulfilling at least two of the Bologna criteria, namely:
an abnormal ovarian reserve test, defined as an AFC of <5–7 follicles and/or AMH level of <0.5–1.1 ng/mL; anda history of poor ovarian response, defined as retrieval of ≤3 oocytes in a previous IVF cycle.

#### Exclusion criteria

Diagnosed of genetic disordersUndergoing treatment for malignancyHistory of bilateral/unilateral oophorectomy or severe systemic illnessParticipation in other clinical trialsContraindications to the Ayurvedic procedures.

## Objectives

Hypothesis: an Ayurvedic treatment protocol might be able to change the ovarian reserve in women diagnosed with DOR, and the pharmacological mechanisms could be investigated through multi-omics approaches.

Exploratory primary objectives:

To evaluate the role of an Ayurveda treatment protocol in improving serum AMH levels and AFC in DOR patients.

Exploratory secondary objectives:

To perform transcriptomics of granulosa cells (GC) in human follicular fluid through RNA sequencing approaches.To identify therapeutic targets of ayurvedic formulations in improving AMH levels through mass spectrometry-based quantitative proteomics.To identify the key metabolites involved in improving serum anti-mullerian hormone levels through untargeted metabolomics of human follicular fluid.

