## Methodology

### Ayurvedic interventions

Women diagnosed with DOR and satisfying the eligibility criteria will be recruited at Amrita Fertility Centre. After due consent, these participants will be subjected to Ayurvedic treatment protocol at Amrita School of Ayurveda.

The intervention protocol begins with śodhana karma (cleansing therapy) and śamana karma (medicines for restoring normalcy or pacifying action). The medicines and formulations selected in the protocol will be individualized according to the participant’s clinical status but follows a standardized therapeutic framework (Table 2).

**Table 2 tab2:** Treatment protocol.

Treatment protocol and interventions—Śodhana karma (cleansing therapy)		
Treatment procedure	Method of administration	Treatment duration
Dīpana, pācana (stimulating digestive fire or appetizing action) with Vaiśvānara cūrṇa (24)	5 g twice daily before food with warm water	Day 1–2
Snehapāna (internal oleation). with appropriate ghee or oil	Ārohaṇakrama (gradually increasing dose) after assessing the agni (digestive, metabolic factors) and koṣṭha (bowel habit)	Day 3–8
Sarvāṅga abhyaṅga and svedana (Oleation and sweating treatment)	Sarvāṅga abhyaṅga (application of oil on whole body) with Dhanvantara taila followed by nāḍīsveda (sweating induced by steam directed from hose)	Day 9–10 for vamana Day 9–day 11 for virecana
Either Vamana (therapeutic emesis) or virecana (therapeutic purgation) (25)	Avipatti choorna 30 g given at 7 a.m. for Virecana	Vamana on Day 10 and Virecana on Day 11
Yogabastiḥ (course of eight combined therapeutic enemas)	Three Nirūhabasti (therapeutic decoction enema) with 750 mL of Mustadiyapanabasti and five anuvasanabasti (therapeutic oil enema) with 150 mL of Mahānārayaṇataila administered on alternate days (26)	Day 13–20
Uttarabasti (administration of therapeutic oil or ghee via vagina)	With 3 mL Mahānārayaṇataila into the uterine cavity on the day of Nirūhabasti	
Śamana karma (medicines for restoring normalcy or pacifying action)		
Medicine	Dose	Time and route of administration
Kalyanaka Ghrita/Phala sarpi (medicated ghee) (27)	10 mL	Morning in empty stomach orally
Mahanarayana taila (medicated oil) (28)	10 mL	Evening in empty stomach orally
Satapushpa choorna/Hinguvachadi choorna (medicines in the form of powder) (29, 30)	5 g	Twice daily before food mixed with ghee in the morning and oil in the evening, orally

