Śodhana karma (cleansing therapy): the participant will be admitted for a maximum of 21 days following the cessation of menstrual bleeding in the first menstrual cycle. The trial intervention begins with dīpana (stimulating digestive fire or appetizing action) and pācana (digestive action) by administering Vaiśvānara Cūrṇa for 2 days. This is intended to enhance the digestive capacity of the participant and prepare them for the subsequent procedure, snehapāna (internal oleation). Snehapāna (internal oleation) is done by the oral administration of medicated ghee or oil in gradually increasing doses until signs of adequate oleation or samyak snigdha lakṣaṇas are observed or for up to a maximum duration of 7 days. The selection of medicine, dose and duration of snehapāna (internal oleation) will be decided based on the agniḥ (digestive, metabolic factors), koṣṭhaḥ (bowel habit) and clinical condition of the participant. Adequate oleation ensures that the body is properly lubricated for detoxification. Snehapāna (internal oleation) is followed by svedana (sudation therapy) which will be performed for 2–3 days which further facilitates the śodhana karma (cleansing therapy). These preparatory procedures together constitute the pūrvakarma (preparatory phase) of śodhana karma (cleansing therapy).

Depending on clinical indications, participants will then undergo vamana (therapeutic emesis) or virecana (therapeutic purgation), which constitute the main śodhana (cleansing) procedures.

In the concluding part of the śodhana karma (cleansing therapy), participants will receive basti karma (therapeutic enema), which involve medicated enemas. Two forms will be administered:

Yogabasti (course of eight combined therapeutic enemas)—a combination of five snehabastiḥ (therapeutic oil enema) and three nirūha basti (therapeutic decoction enema) given alternately over 8 days.Uttarabasti (administration of therapeutic oil or ghee via vagina)—will be performed on the same day as the nirūha Basti, aimed at directly nourishing and rejuvenating the reproductive organs and their functions.

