Śamana karma (medicines for restoring normalcy or pacifying action): following cleansing, participants will begin the śamana cikitsā, consisting of orally administered Ayurvedic formulations for 1 month. These formulations are specifically intended to improve ovarian function and reproductive health by restoring ārtava upadhātu (the supportive component of reproductive system). The selection of medicines will be based on the condition of the patient. All medicines used during the treatments will be procured from a GMP-certified company. To ensure uniformity, the project research scientist who is a specialist doctor will be adhering strictly to the standard operating procedures of the study centre. Participant adherence to the Ayurvedic treatment protocol will be closely monitored throughout the study period using patient file, medication diary, weekly telephonic reminders and digital communication. After undergoing Ayurveda treatment for approximately 2 months, participants will be sent back to Amrita Fertility Centre for post-assessment and further fertility treatments, during which follicular fluid will be collected for multi-omics analysis.

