Follicular fluid from 10 control participants and 10 Ayurvedic-treated participants chosen from the 30-participants treatment arm and matched according to age and baseline AMH/AFC will be obtained for the secondary, exploratory multi-omics analysis. All the laboratory experiments will be performed in triplicates (of each biological samples) and statistical analysis will be done using GraphPad Prism software. The statistical analysis of collected proteome data will be performed using Proteome Scaffold software (version 4). Peptide identifications will be accepted if they can be established at greater than 95.0% probability. The Scaffold Local FDR algorithm and peptide prophet algorithm with scaffold delta-mass correction will assign peptide probabilities. Protein identifications will be accepted if they can be established at greater than 99.0% probability and contain at least two peptides representing the protein family. The protein prophet algorithm will assign protein probabilities (34, 35). For metabolomics analysis, after data generation, the heatmaps, principal component analysis, and multivariate statistical analysis will be performed using R (Version 4.5.1) and MetaboAnalyst 6.0. To evaluate the differences between the treatment and control groups in transcriptomics, proteomics, and metabolomics, *t*-tests (for normally distributed data) or Mann–Whitney U tests (for non-normal data) will be used for each gene, protein, or metabolite. To account for multiple comparisons, the Benjamini–Hochberg FDR correction will be used; an FDR of less than 0.05 will be considered significant. As described under each section, specific assays will be used to further validate the most important genes and proteins. No formal sample size calculation was performed for the exploratory multi-omics analysis, as it is hypothesis-generating, and the 10 treatment samples were selected based on matching and feasibility.

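### The proteomics objective asks for targets of formulations, but the 10 v 10 comparison can speak only to the whole Ayurvedic treatment programme

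*Protocol article*

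**What the plan says.** The Objectives section of the protocol article gives the proteomics objective as "To identify therapeutic targets of ayurvedic formulations in improving AMH levels through mass spectrometry-based quantitative proteomics". The exposure it names is formulations.

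The Ayurvedic interventions section describes what treated women receive:

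- On the programme overall: "The medicines and formulations selected in the protocol will be individualized according to the participant’s clinical status but follows a standardized therapeutic framework".
- On the main cleansing step: "Depending on clinical indications, participants will then undergo vamana (therapeutic emesis) or virecana (therapeutic purgation".
- On the month of oral medicines: "The selection of medicines will be based on the condition of the patient". Table 2 lists two ghees, "Kalyanaka Ghrita/Phala sarpi (medicated ghee", and two powders, "Satapushpa choorna/Hinguvachadi choorna".
- The agent, dose and duration of internal oleation are set for each woman. Table 2 allows a ghee or an oil and names no product.
- Other items appear in Table 2 with no alternative: Vaiśvānara cūrṇa, Dhanvantara taila, the enema materials and Mahānārayaṇa taila.

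Sample size and Statistical methods define the omics comparison: follicular fluid from 10 treated women and from 10 controls undergoing IVF without the programme, matched on age and baseline AMH/AFC, with each gene, protein or metabolite tested between the two groups. On how the treated samples are picked: "the 10 treatment samples were selected based on matching and feasibility". No component of the regimen enters the selection or the test.

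**The concern.** The objective asks which proteins are targets of particular medicines. The design has one exposure contrast: everything in the programme against none of it. If the objective stands as worded, a protein that differs between the groups could be reported as a target of the formulations. It might instead reflect the emesis or purgation, the enemas, the sweating treatment, the inpatient stay, or a difference between two non-randomised groups. It might also be credited to a ghee or powder that only some of the ten women took. Later work planned on such a claim would start from an attribution that the data could not have supported.

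**Working it through.** The omics part has no calculated figure to reproduce; the article says that no formal calculation was made for it. The article's only calculated sample size, 26, belongs to the within-woman AMH/AFC change and does not bear on this point.

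**Step 1. What the contrast estimates.** The test compares the mean of each protein in treated women with its mean in controls. Every component common to all treated women is present in all ten of them and, as part of the programme, in none of the controls. These components coincide exactly with the group indicator, so none can be separated from another. This would hold even if every woman had an identical regimen.

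**Step 2. What individualisation adds.** The optional components vary only within the treated ten, they follow clinical condition, and no comparison between them is planned. The treated mean is therefore an average over whatever mix of regimens occurs. Matching on age and baseline AMH/AFC does not cover the clinical reasons for each choice.

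**Step 3. How many regimens are permitted.** Reading each slash in Table 2 as alternatives:

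- main procedure 2 x ghee 2 x powder 2 = 8;
- with oleation counted as ghee or oil, 8 x 2 = 16, or more because the product is not named.

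**Step 4. How many might occur among ten women.** The documents give no choice frequencies, so the splits below are assumptions, with the choices taken as independent. For k equally likely regimens the expected number in use is k x (1 − (1 − 1/k)^10):

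- k = 8: 8 x (1 − 0.875^10) = 5.9;
- k = 16: 16 x (1 − 0.9375^10) = 7.6.

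For unequal splits the expected number is the sum over the 8 combinations of 1 − (1 − p)^10. If each choice has a split q to 1 − q, the combination of the three commoner options is expected to hold 10 x q³ women.

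| Split on each of three choices | Expected regimens in use (of 8) | Women expected on the combination of commoner options |
|---|---|---|
| 50/50 | 5.9 | 1.25 (no combination is favoured) |
| 70/30 | 5.0 | 3.4 |
| 80/20 | 4.1 | 5.1 |
| 90/10 | 3.0 | 7.3 |

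With even choices, the chance that all 8 combinations occur among ten women is 0.028, and the largest group averages about 3 women. At 90/10 the commonest combination has probability 0.9³ = 0.729, so the chance that all ten women share it is 0.729^10, about 4%. Some mixing is likely under each of these splits, but its extent is not known.

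**The case against.** The strongest reply is that the word formulations is meant collectively. The Introduction speaks of mechanisms induced by Ayurvedic treatment, the hypothesis in Objectives refers to a treatment protocol, and the Outcomes section promises only altered protein profiles. The objectives are labelled exploratory, the omics part is called hypothesis-generating, and clinical inference between the groups is ruled out. Individualisation also stays inside a standardised framework with several products common to all women.

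Most of this stands, and it is why the point is minor. It does not rescue the wording. Even read collectively, formulations leaves out the procedures, which are part of the same contrast. The exploratory label excuses the absence of a sample size calculation; it does not supply a link between a protein and a medicine.

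Three stronger readings are tempting but not supported:

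- A reader might infer that the ten samples will be spread over eight or more regimens. Eight is a count of permitted combinations. The realised spread is unknown, and with eight combinations all would rarely be used.
- A reader might infer that individualisation is what defeats attribution. Step 1 shows that a fixed regimen would be confounded as well; individualisation only adds to the problem.
- A reader might want all ten treated women taken from one main procedure. That is not recommended. It would select treated women on clinical indication with no such limit on controls, and it still would not isolate a formulation. Ten women from one procedure are guaranteed only if at least 19 treated women reach oocyte retrieval, before any matching.

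**Conclusion.** Wrong as written, and minor. An exploratory secondary objective asks a formulation-level question that the design cannot answer; the data can show only protein differences associated with the programme as a whole. This conclusion rests on the components being given together and on the single treated-control contrast, both of which the article states. It does not depend on any assumption about how often each option is chosen. The regimen counts (8 permitted, or 16 and more with oleation; about 3 to 6 of the 8 expected among ten women) do depend on reading the slashes as alternatives and on the assumed independent splits. Individualisation may also add between-woman variance to the 10 v 10 test, but the documents give nothing from which to size it. The comparison keeps its value as a hypothesis-generating look at the programme.

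**What to change.** Reword the second exploratory secondary objective along these lines: to explore protein differences in follicular fluid associated with the Ayurvedic treatment programme. State that conclusions from the omics comparison will be drawn at that level only. This brings the objective into line with the Introduction and the stated hypothesis.

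When results are reported, list descriptively beside each omics sample the main procedure and medicines that the woman received. The patient file and medication diary described in the article should already hold this information.

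The cost is a change of wording and one descriptive listing. No woman's treatment, the selection of samples, the sample size and the laboratory work are unaffected. What is given up is the claim to have found targets of specific formulations, which would need a design that separates the components.

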## Outcomes

Exploratory primary outcome

1 (a). Change in serum AMH.

Time frame:

Assessment before treatment (BT)—on day2/3 of the first menstrual cycle during recruitmentpost assessment (AT)—on Day 2/3 of the third menstrual cycle that comes after 2 months of Ayurvedic treatment

1 (b). Improvement in ultrasonography count of ovarian antral follicles, AFC.

Time frame:

Assessment before treatment (BT)—on day2/3 of the first menstrual cycle during recruitmentPost assessment—on Day 2/3 of the third menstrual cycle that comes after 2 months of Ayurvedic treatment

Exploratory secondary outcomes.

Multi omics analysis of follicular fluid—(Treatment group—10; after 2 months of Ayurveda treatment and Control group—10).

Time frame: day of oocyte retrieval of the IVF cycle.

2. The genes involved in improving the treatment outcomes can be determined through transcriptomics analysis.3. Through quantitative proteomics, the altered protein profiles can be estimated.4. Metabolomics approaches enable in the identification of key metabolites involved in improving treatment outcomes in DOR patients.

## Methodology

### Ayurvedic interventions

Women diagnosed with DOR and satisfying the eligibility criteria will be recruited at Amrita Fertility Centre. After due consent, these participants will be subjected to Ayurvedic treatment protocol at Amrita School of Ayurveda.

The intervention protocol begins with śodhana karma (cleansing therapy) and śamana karma (medicines for restoring normalcy or pacifying action). The medicines and formulations selected in the protocol will be individualized according to the participant’s clinical status but follows a standardized therapeutic framework (Table 2).

**Table 2 tab2:** Treatment protocol.

Treatment protocol and interventions—Śodhana karma (cleansing therapy)		
Treatment procedure	Method of administration	Treatment duration
Dīpana, pācana (stimulating digestive fire or appetizing action) with Vaiśvānara cūrṇa (24)	5 g twice daily before food with warm water	Day 1–2
Snehapāna (internal oleation). with appropriate ghee or oil	Ārohaṇakrama (gradually increasing dose) after assessing the agni (digestive, metabolic factors) and koṣṭha (bowel habit)	Day 3–8
Sarvāṅga abhyaṅga and svedana (Oleation and sweating treatment)	Sarvāṅga abhyaṅga (application of oil on whole body) with Dhanvantara taila followed by nāḍīsveda (sweating induced by steam directed from hose)	Day 9–10 for vamana Day 9–day 11 for virecana
Either Vamana (therapeutic emesis) or virecana (therapeutic purgation) (25)	Avipatti choorna 30 g given at 7 a.m. for Virecana	Vamana on Day 10 and Virecana on Day 11
Yogabastiḥ (course of eight combined therapeutic enemas)	Three Nirūhabasti (therapeutic decoction enema) with 750 mL of Mustadiyapanabasti and five anuvasanabasti (therapeutic oil enema) with 150 mL of Mahānārayaṇataila administered on alternate days (26)	Day 13–20
Uttarabasti (administration of therapeutic oil or ghee via vagina)	With 3 mL Mahānārayaṇataila into the uterine cavity on the day of Nirūhabasti	
Śamana karma (medicines for restoring normalcy or pacifying action)		
Medicine	Dose	Time and route of administration
Kalyanaka Ghrita/Phala sarpi (medicated ghee) (27)	10 mL	Morning in empty stomach orally
Mahanarayana taila (medicated oil) (28)	10 mL	Evening in empty stomach orally
Satapushpa choorna/Hinguvachadi choorna (medicines in the form of powder) (29, 30)	5 g	Twice daily before food mixed with ghee in the morning and oil in the evening, orally

Śodhana karma (cleansing therapy): the participant will be admitted for a maximum of 21 days following the cessation of menstrual bleeding in the first menstrual cycle. The trial intervention begins with dīpana (stimulating digestive fire or appetizing action) and pācana (digestive action) by administering Vaiśvānara Cūrṇa for 2 days. This is intended to enhance the digestive capacity of the participant and prepare them for the subsequent procedure, snehapāna (internal oleation). Snehapāna (internal oleation) is done by the oral administration of medicated ghee or oil in gradually increasing doses until signs of adequate oleation or samyak snigdha lakṣaṇas are observed or for up to a maximum duration of 7 days. The selection of medicine, dose and duration of snehapāna (internal oleation) will be decided based on the agniḥ (digestive, metabolic factors), koṣṭhaḥ (bowel habit) and clinical condition of the participant. Adequate oleation ensures that the body is properly lubricated for detoxification. Snehapāna (internal oleation) is followed by svedana (sudation therapy) which will be performed for 2–3 days which further facilitates the śodhana karma (cleansing therapy). These preparatory procedures together constitute the pūrvakarma (preparatory phase) of śodhana karma (cleansing therapy).

Depending on clinical indications, participants will then undergo vamana (therapeutic emesis) or virecana (therapeutic purgation), which constitute the main śodhana (cleansing) procedures.

In the concluding part of the śodhana karma (cleansing therapy), participants will receive basti karma (therapeutic enema), which involve medicated enemas. Two forms will be administered:

Yogabasti (course of eight combined therapeutic enemas)—a combination of five snehabastiḥ (therapeutic oil enema) and three nirūha basti (therapeutic decoction enema) given alternately over 8 days.Uttarabasti (administration of therapeutic oil or ghee via vagina)—will be performed on the same day as the nirūha Basti, aimed at directly nourishing and rejuvenating the reproductive organs and their functions.

Śamana karma (medicines for restoring normalcy or pacifying action): following cleansing, participants will begin the śamana cikitsā, consisting of orally administered Ayurvedic formulations for 1 month. These formulations are specifically intended to improve ovarian function and reproductive health by restoring ārtava upadhātu (the supportive component of reproductive system). The selection of medicines will be based on the condition of the patient. All medicines used during the treatments will be procured from a GMP-certified company. To ensure uniformity, the project research scientist who is a specialist doctor will be adhering strictly to the standard operating procedures of the study centre. Participant adherence to the Ayurvedic treatment protocol will be closely monitored throughout the study period using patient file, medication diary, weekly telephonic reminders and digital communication. After undergoing Ayurveda treatment for approximately 2 months, participants will be sent back to Amrita Fertility Centre for post-assessment and further fertility treatments, during which follicular fluid will be collected for multi-omics analysis.

